#### Randomization

2.9.4

There will be 8 clusters of patients to be randomised (4 × 2 dyads) organised by location of dialysis (TUH or NW), day of the week (Monday-Wednesday-Friday roster or Tuesday-Thursday-Saturday roster) and time of dialysis (morning or afternoon). Randomization will be to VR (intervention) or usual activities (control) (Fig. 1).

**Fig. 1 fig1:**
[figure not shown]
Design of Cross-over Randomised Controlled feasibility study.

To avoid contamination, clusters will be randomised (using web-based computer program, for example www.randomization.com) [27] within dyads as to which cluster receives VR first. Whilst it is not possible to ‘blind’ participants and unit staff to the allocation, the investigators analysing the data will be blinded to group assignment.

#### Data collection processes

2.9.5

So as not to inconvenience patient participants' routines, the conversational interview about their experiences with VR, and the data related to quality of life and psychological measures will take place during a scheduled dialysis session (in the week following the 4-week intervention/control periods). All data collected directly from the participants will be undertaken in a conversational manner in their familiar surroundings. If the patient prefers, data collection can be undertaken in an office in the renal unit; it is recognised, however, that this would be a less inviting environment and may inhibit conversation. Measures to be used are described earlier in sections 2.9.1.2, 2.9.1.3, and 2.9.1.4. After recruitment and consent, but before their first haemodialysis session associated with the trial, participants will be asked to complete the AQoL-6D and the K-5 at three timepoints: the week prior to first haemodialysis session associated with the trial, the one-week ‘washout period’ between the intervention and control phase (or vice versa) and in the week following involvement in the trial. (Refer to Fig. 1). During the intervention phase, the research assistant/Health Workers/nurses will seek formative feedback about the use of the VR headset. The summative interview (based on the User Engagement scale) will be conducted in the week following completion of the intervention period.

Socio-demographic and clinical related characteristics of participants such as age, gender, relationship status, place of residence, age at initiation of haemodialysis, type of vascular access, cause of renal failure) will be obtained from the participants' medical records by the study's Research Assistant, after patient consent has been obtained. Attendance and intradialytic weight gain will be retrieved from the electronical medical record for each dialysis session.

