### Project outcomes

2.9

The primary outcome is attendance at scheduled dialysis sessions.

The secondary outcomes are:-Adherence to fluid allowances between dialysis sessions;-Health related quality of life;-Engagement with self-care;-Depression and anxiety;-Usage, acceptability and usability of VR; and-Participants' (patients and clinicians) satisfaction with VR.

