##### Adherence to haemodialysis regimens will be measured by

2.9.1.1

-difference in participants' attendance rates when in the intervention phase compared to the control (non-intervention) phase; and-difference in proportions of participants' adherence to fluid allowances, defined as gaining, on average, no more than 1 kg per day between dialysis sessions in the intervention phase compared to the control phase [2].

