A Participant Information Sheet and Consent Form will be provided to all potential participants. These documents can be read to potential participants if required. Written consent will be obtained by the patient signing with their name or an X. Participants’ consent will be requested for the collection of demographic characteristics such as: age; ethnicity; living arrangements (whether it is shared accommodation (hostel) or private house; social supports; whether the patient has had to relocate to Townsville for dialysis; distance travelled each day for dialysis); length of time since commenced on dialysis; duration of each dialysis session; intradialytic weight gain and attendance records. Previous research conducted in the renal unit by this team has been successful in terms of participant recruitment [for example, 19].

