#### Data management and storage

2.9.6

Patients participating in the study will have a unique study number assigned to them. Data pertaining to conversational interviews with the patient participant group will have identifiers removed following analysis. Data pertaining to attendance, intradialytic weight gain, and psychological measures will be re-identifiable at collection; identifiers will be removed following data cleaning and analysis. Anonymous survey data from the clinicians will be collected electronically through the survey tool hosted on the Qualtrics platform. Partially completed survey responses will be included. The Qualtrics survey data will be hosted on the James Cook University server. Other study documents will be stored at TUH.

All data obtained will remain confidential and will be securely stored throughout the course of the study within locked cupboards/filing cabinets, to which only the research team members have access. Computer files will be accessible only to the research team. Participants in the trial will not be identifiable in any reports, publications or presentations arising from the study. This study has ethics approval from the Health service's Human Research and Ethics Committee (HREC/QTHS/72273).

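### The fluid outcome is weight gained between sessions, but the data item is named intradialytic gain, and the stated comparison uses only proportions at a 1 kg/day cut

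*Protocol article*

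**What the plan says.** Section 2.9 (Project outcomes) lists as a secondary outcome "Adherence to fluid allowances between dialysis sessions". Section 2.9.1.1 makes it operational as a "difference in proportions of participants' adherence to fluid allowances", "defined as gaining, on average, no more than 1 kg per day between dialysis sessions", compared between the intervention and control phases.

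The data item appears in three places, under the same name each time:

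- Section 2.9.2.1, among the items for which consent is requested: "intradialytic weight gain and attendance records".
- Section 2.9.5, the extraction instruction: "Attendance and intradialytic weight gain will be retrieved from the electronical medical record for each dialysis session".
- Section 2.9.6, data handling: "Data pertaining to attendance, intradialytic weight gain, and psychological measures".

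Interdialytic gain is not named anywhere, nor are pre-dialysis weight, post-dialysis weight or the days between sessions as items to extract. Section 2.9.7 assigns chi-square tests to categorical data and paired t-tests or ANOVA to continuous data. No continuous weight-gain outcome is defined for the latter to apply to.

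**The concern.** There are two linked problems.

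First, the outcome and the data item describe different quantities. The outcome concerns fluid gained between treatments, whereas intradialytic change is what happens during a treatment. A research assistant who follows section 2.9.5 to the letter would extract a variable that does not answer the secondary objective.

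Second, the stated comparison reduces a numeric measurement, available at up to 12 sessions per phase, to whether a cut-off was met. With 40 patients this can cost much of the precision. It also leaves the later trial without the spread and within-person correlation of the underlying measurement, and section 1.1 gives informing that trial as an aim.

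**Working it through.** **1. Can the outcome be obtained from the named item?**

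For session k, write Pre(k) and Post(k) for the weights before and after dialysis.

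- Outcome: gain per day = [Pre(k) − Post(k−1)] / days since the previous attended session.
- Item as named: within-session change W(k) = Post(k) − Pre(k).
- Rearranging: Pre(k) − Post(k−1) = [Post(k) − Post(k−1)] − W(k).

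So W(k) gives the between-session gain (with the sign reversed) only if the patient leaves consecutive sessions at the same weight. The number of days is needed as well. On the rosters in section 2.9.4 the gap is 2 or 3 days with full attendance, and 4 days or more if a session is missed. Attendance is itself the primary outcome, so the divisor should be the actual gap and not the scheduled one.

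**2. How much does the yes/no form cost?**

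The plan has no calculation to reproduce. Section 2.8 says the sample size rests on similar studies and practical limits. The figures that can be checked agree: 8 clusters × 5 = 40 patients, and 4 weeks × 3 = 12 sessions per phase.

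Inputs not in the documents, hence assumed: the share adherent, p (0.5 to 0.8), and the correlation of a participant's mean gain between phases, ρ (0.3 to 0.7). The model is bivariate normal, and clustering and period effects are ignored.

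*Reading A: one yes/no per participant per phase.* With c the normal quantile of p, φ(c) the normal density there, and r the correlation of the two yes/no values:

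information kept = {φ(c)² / [p(1−p)]} × (1−ρ)/(1−r)

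At p = 0.5 the first factor is 0.1592/0.25 = 0.637. At p = 0.8 it is 0.0784/0.16 = 0.490.

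| p | ρ | r | (1−ρ)/(1−r) | Information kept |
|---|---|---|---|---|
| 0.5 | 0.3 | 0.194 | 0.868 | 55% |
| 0.5 | 0.5 | 0.333 | 0.750 | 48% |
| 0.5 | 0.7 | 0.494 | 0.592 | 38% |
| 0.8 | 0.3 | 0.163 | 0.837 | 41% |
| 0.8 | 0.5 | 0.295 | 0.709 | 35% |
| 0.8 | 0.7 | 0.456 | 0.551 | 27% |

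The yes/no form would therefore need between 1/0.55 = 1.8 and 1/0.27 = 3.7 times as many participants for the same precision.

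A simulation (20,000 runs, n = 40, two-sided 0.05) used a shift chosen for nominal 80% power on the continuous scale. The paired t-test reached about 78%. McNemar's test without continuity correction reached 51%, 45% and 35% at p = 0.5, and 31%, 28% and 24% at p = 0.8 (ρ = 0.3, 0.5, 0.7).

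*Reading B: a proportion of adherent intervals per participant per phase.* Take 12 intervals, within-phase correlation w (0.3 to 0.7) and between-phase correlation b of the person effects (0.6 to 0.8), all assumed. With C(x) the covariance of two yes/no values whose underlying correlation is x:

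information kept = φ(c)² × [w + (1−w)/12 − wb] / [p(1−p)/12 + (11/12)·C(w) − C(wb)]

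Example at p = 0.5, w = 0.5, b = 0.7, where C(x) = asin(x)/(2π): the numerator is 0.1592 × 0.1917 = 0.0305, the denominator is 0.0208 + 0.0764 − 0.0569 = 0.0403, and the ratio is 76%. Over the stated ranges, with p = 0.5 or 0.8, the result runs from about 50% to 80%.

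**The case against.** The strongest reply is that *intradialytic* is a slip of terminology. The outcome is stated clearly, dialysis removes fluid so a *gain* makes sense only between sessions, and the item is retrieved to serve that outcome. This stands. A reader might infer that the wrong variable will be collected, but the documents do not show that. What remains is that the same term is used in all three places, including the extraction instruction, so it is wrong text and not a detail left to a fuller document.

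A reader might also infer that most of the information is lost. That depends on unstated inputs and on Reading A. Near a median split with ρ of 0.4 or less, slightly more than half is kept (52% to 55%), and under Reading B the loss is smaller. Nor is anything lost at collection: values are retrieved per session and section 2.9.7 already allows paired t-tests, so a continuous analysis stays open.

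Two further inferences do not hold on this text. One is that gain measured at the first session of a phase is credited to the wrong phase; the article gives neither an attribution rule nor a start day, and such detail is commonly left to a fuller document. The other is that participants consent to the wrong item; section 2.9.2.1 only gives examples of items, and the consent form is not shown.

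Finally, the 1 kg/day cut is referenced to earlier work, the outcome is secondary, and section 2.8 puts less weight on hypothesis testing. This limits the severity. It does not remove the point, because the same section stresses whether the measures are applicable in this population.

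**Conclusion.** The inconsistency of terms is certain from the text: a between-session outcome against a data item named as within-session in three places out of three. Its practical effect is uncertain, since a misnomer is the likelier explanation.

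The cost of the yes/no comparison is real, but its size is conditional. It keeps roughly 27% to 55% of the information if each participant contributes one yes/no per phase (p 0.5 to 0.8, ρ 0.3 to 0.7), and roughly 50% to 80% if each contributes a proportion of adherent intervals. All these inputs are assumptions, under a normal model without cluster or period effects. The loss lies in the outcome definition and can be recovered.

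Severity is minor to moderate.

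**What to change.** - In sections 2.9.2.1, 2.9.5 and 2.9.6, replace the term with *interdialytic weight gain*.
- State the derivation: pre-dialysis weight minus the previous post-dialysis weight, divided by the actual days between attended sessions. It would help to say at the same time which intervals count towards each phase.
- Analyse mean kg/day per phase as a continuous within-participant comparison, and report the proportion gaining no more than 1 kg/day beside it. Say whether that proportion is of participants or of intervals.
- Report the standard deviation and between-phase correlation of mean kg/day for use in planning the multi-centre trial.

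The cost is a wording change, a little extra extraction from the routine record, and one more analysis. No new procedure or patient contact is involved, and the threshold-based measure is kept for comparison with earlier work.

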##### Data collection/gathering techniques and information to be gathered relating to conversational semi-structured interview with patients

2.9.5.1

Conversational semi-structured interviews will be conducted with the patient participants. The Clinical Nurse Consultant – Indigenous at TUH, has reviewed and approved the questions on the interview schedule as being culturally and linguistically appropriate. The Health Workers – Renal and Research Assistants will be provided training/practice to undertake the conversational interviews. To allow flexibility and spontaneity during the interviews, interview questions may not be asked in the same order or wording as in the interview guide. However, all questions in the interview guide will be discussed during each interview. Questions relating to any difficulties encountered while using the VR headset, experience of any kind of motion sickness will be included.

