**Methods:**

The design is a crossover RCT, with 8 clusters according to haemodialysis location and schedule. Clusters (5 participants in each) will be randomized by computer program. Participants in the trial will be patients who undergo haemodialysis three times/week at one of two dialysis units. During the 4-week intervention period (12 haemodialysis sessions), participants will be provided a headset with vision representative of the natural environment, and with audio. The 4-week control period will comprise usual activities, such as watching television, reading and sleeping. Outcomes will be measured by participants': attendance at scheduled dialysis sessions; adherence to lifestyle modifications; wellbeing, anxiety and depression; acceptability and usability of VR; and adverse events such as nausea. The feasibility and acceptability of the intervention from clinicians’ perspectives will also be explored.

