### Background

**1.1**

Immersive VR, where a person is exposed to video and sound via a head-mounted display and is isolated from the external world [7], has been shown to be more effective across different domains and settings than traditional two-dimensional (2D) or three-dimensional (3D) video. For example, participants reported greater ‘presence’ when playing a video game in immersive VR format compared to 2D or 3D formats [8], and a greater sense of awe [9,10], and better cognitive function (memory) [11]. Findings from randomised controlled trials (RCTs) of VR in haemodialysis sessions have produced different responses with respect to depression. Non-immersive virtual reality combined with exercise significantly reduced depression in a sample of patients undergoing haemodialysis in Qatar [12] but had no effect in a similar study undertaken in Brazil [13]; different measurement tools were used [6].

It is acknowledged that VR may have the potential to evoke nausea or a sense of motion sickness, as identified by a crossover observational study involving volunteers watching 3D movies [14]. However, a quasi-experimental study undertaken in a haemodialysis setting [15] demonstrated that immersive VR did not worsen a participant's usual symptoms of headaches or nausea. A recent systematic review identified that VR was generally acceptable and safe in a haemodialysis setting, although most studies have used non-immersive VR to promote exercise [6].

Haemodialysis units are clinical, medicalised environments. It is proposed that a VR intervention that is engaging, such as the opportunity to ‘travel through landscapes’, will enable a person to feel more at ease and disengaged from the aspects of the surrounding treatment environment which may arouse anxiety.

The aims of this study are to explore the feasibility of an immersive VR experience for patients undergoing haemodialysis; and to inform a multi-centred RCT on the effects of VR for patients undergoing haemodialysis.

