##### Participants' satisfaction, usage and usability, and clinicians’ satisfaction measurements

2.9.1.4

Participants' satisfaction with, and immersion in, the VR experience will be measured with the User Engagement Scale – Short Form [24], modified and incorporated into a conversational interview, congruent with a ‘yarning’ method of Indigenous research [25]. Usage and usability of the VR will be measured by the percentage of dialysis occasions that patients use the VR headset, the amount of time within a session the participant used the headset, whether VR is used at the beginning, middle or towards the end of the dialysis sessions. These data are gathered by the headset and uploaded automatically from it. Any difficulties encountered in its use will be likely reported in the delivery of the User Engagement scale above.

Clinicians’ satisfaction will be measured by a questionnaire asking about the acceptability, feasibility, benefits and barriers to using VR in a haemodialysis setting. Due to the novelty of VR in treatment environments, no appropriate standardised assessments for this population group using this technique currently exist. Clinical staff will be asked to complete a survey adapted from Lindner et al. [26]. This assessment asks about clinician familiarity with the medium both in and outside the clinical setting. Respondents are presented with positive and negative aspects of the use of VR (e.g. patient mood improvement versus cost of technology) and asked how concerned they are about each issue. There is an option at the end of the questionnaire for open-ended answers for additional comments.

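### Adverse events are an outcome in the abstract but not in the outcome list, and no symptom measure is described for the control phase, so symptoms cannot be compared between phases

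*Protocol article*

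**What the plan says.** The abstract's methods paragraph ends its list of measured outcomes with "acceptability and usability of VR; and adverse events such as nausea". Section 2.9 then sets out the outcomes formally. It states that "The primary outcome is attendance at scheduled dialysis sessions", and its secondary list runs from fluid adherence, quality of life, self-care, and depression and anxiety to "Usage, acceptability and usability of VR; and-Participants' (patients and clinicians) satisfaction with VR". Neither that list, nor the objectives in section 2.1, nor the measures in section 2.9.1 include an adverse-event or symptom outcome.

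Symptoms appear in the section on the patient interview (2.9.5.1): "Questions relating to any difficulties encountered while using the VR headset, experience of any kind of motion sickness will be included". Section 2.9.5 fixes the timing: "The summative interview (based on the User Engagement scale) will be conducted in the week following completion of the intervention period". Section 2.9.1.4 adds, of the headset, "Any difficulties encountered in its use will be likely reported in the delivery of the User Engagement scale above".

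Section 2.9.1 says that every outcome is compared between the intervention and control phases within participants. The background (section 1.1) acknowledges that VR may provoke nausea or motion sickness. It also cites a quasi-experimental study in haemodialysis in which immersive VR did not worsen participants' "usual symptoms of headaches or nausea".

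**The concern.** The document carries two different outcome sets, and the one that includes adverse events has no matching measure. The stated symptom question is tied to VR and asked once, after the VR period. Nothing corresponding is described after the control period.

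The crossover gives each participant a control phase. For symptoms that phase is the natural yardstick, because patients on dialysis may feel nauseated or have headaches without any headset. If symptoms are counted only around VR, the count mixes what dialysis produces with what VR adds. Tolerability is a central result for a feasibility study meant to inform a multi-centre trial. Section 1.1 also notes that most of the earlier VR studies in haemodialysis used non-immersive VR.

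**Working it through.** **1. Setting the sections side by side**

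| Place | Adverse events or symptoms? |
|---|---|
| Abstract, methods | Yes, as a measured outcome |
| 2.1 Objectives | No |
| 2.9 Outcomes | No |
| 2.9.1.1 to 2.9.1.4 Measures | No symptom measure; difficulties in use are expected to surface with the User Engagement Scale |
| 2.9.5 Collected for both phases | Attendance and weight gain per session; AQoL-6D and K-5 at baseline, in the washout week and in the week after the trial. No symptoms |
| 2.9.5 VR phase only | Formative feedback on headset use, not stated to cover symptoms; interview after the VR period |
| 2.9.5.1 Interview | Headset difficulties and motion sickness; order and wording may vary |
| 2.9.8 Safety | Usual nurse monitoring; concerns go to the Stakeholder Group and treating clinician |

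No row gives a symptom measure for the control phase, so the paired comparison of section 2.9.1 has only one side.

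**2. Inputs for the size**

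- Participants: 8 clusters × 5 = 40, which reproduces the sample size in section 2.8.
- Sessions per phase: 4 weeks × 3 per week = 12, as in the abstract.
- Background nausea: the document gives no rate. I assume that it occurs in 5% to 15% of sessions.

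**3. Participants with at least one episode in 12 sessions and no VR effect**

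The answer depends on how far episodes fall in the same patients, so both extremes are shown.

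- Independent sessions, 1 − (1 − p)^12:
  - p = 0.05: 1 − 0.95^12 = 0.46; × 40 ≈ 18 participants.
  - p = 0.15: 1 − 0.85^12 = 0.86; × 40 ≈ 34 participants.
- Full clustering (the same patients are affected at every session), share = p:
  - p = 0.05: 0.05 × 40 = 2 participants.
  - p = 0.15: 0.15 × 40 = 6 participants.

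**4. A check that makes no assumption about sessions**

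Suppose a fraction q of the 40 participants would report nausea in any four-week period without VR. The number of reports is taken as binomial (40, q), that is, independent between participants.

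| q (assumed) | Expected reports, 40q | Chance of 5 or more |
|---|---|---|
| 5% | 2 | 0.05 |
| 10% | 4 | 0.37 |
| 20% | 8 | 0.92 |
| 30% | 12 | 0.997 |

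Five reports after the VR phase would be surprising if the background were 5% and expected if it were 20%. Only a control-phase count from the same participants would show which applies.

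**The case against.** The strongest reply is that symptoms are not left to a single recall interview. Staff seek formative feedback during the VR phase. Nurses fit the headsets and are there to remove them. Safety concerns go to the Stakeholder Group, which meets at least monthly, and its notes and the investigators' observational notes enter the analysis (sections 2.9.5, 2.9.7 and 2.9.8). This stands: symptoms during VR may well be noticed. But none of these channels is described as a symptom record, and none is described as supplying a count for the control phase.

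A reader might infer that VR symptoms cannot be told from dialysis symptoms at all. The document does not support that. The interview asks about headset difficulties and motion sickness, not nausea in general. The simulations last 30 to 40 minutes within sessions of at least 3 hours, and the headset logs when it is used. A participant can attribute a symptom to the headset. What is missing is narrower: a comparison between phases. For the same reason, the figures for any nausea in step 3 are not a forecast of what the interview will return.

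A reader might also infer that people who leave because of symptoms will be missed. That is a possibility only. Participants may decline the headset on any day without leaving the study, and data collected before withdrawal are kept (section 2.9.3). No interview at withdrawal is described, however.

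Finally, the full protocol may hold an adverse-event form or an interview guide that the article condenses. The lack of a per-session form here is therefore weak evidence that none exists. The mismatch between the abstract and section 2.9 does not depend on this, because both texts are shown.

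**Conclusion.** The concern holds in limited form. The abstract and section 2.9 disagree on whether adverse events are an outcome. As described, symptoms cannot be compared between the VR and control phases within participants, which is the comparison that section 2.9.1 promises.

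The size is uncertain. With assumed nausea in 5% to 15% of sessions, anything from 2 to 34 of 40 participants would have at least one episode in 12 sessions without any VR effect, depending on the rate and on clustering within patients. The upper end needs independence between sessions, which is unlikely if the same patients tend to be affected. The conclusion does not need the upper end: a count from the VR phase alone is hard to interpret across the range.

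It would go too far to say that the trial can learn nothing about tolerability. Usage logs, interviews, staff notes and the clinician survey all bear on it. The study is also a feasibility study with little weight on hypothesis testing (section 2.8), so a descriptive comparison is enough.

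**What to change.** 1. List symptoms and adverse events as a safety outcome in section 2.9, in agreement with the abstract.
2. Ask the same short set of symptom questions (for example nausea, headache, dizziness), in fixed wording, at the contacts already scheduled for the AQoL-6D and K-5 in the week after each four-week period. Ask them at withdrawal too, where possible.
3. Compare VR with control within participant, descriptively.

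This costs some protocol wording and a few extra questions per contact. Its limit is that the answers are unblinded recall. It should be in place before data collection, because control-phase symptoms that were never asked about cannot be recovered reliably.

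Recording symptoms at every session in both phases is an optional addition. It would reduce reliance on recall, but it adds up to 2 × 12 × 40 = 960 session records, and unblinded nurses may record more readily in VR sessions.
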